## **6. Methods**

### **PARTICIPANTS, INTERVENTIONS, AND OUTCOMES**

#### **6.1. Study setting**

This study will be carried out in the primary care setting involving community pharmacies and Family health Units (FHU) in Portugal mainland.

FHUs' collaboration for the intervention arm development was established with two FHUs from the Health Centres Group - ACES Alto Minho/ULSAM in Viana do Castelo district, which showed interest to participate in a community pharmacist-general practitioner collaborative trial in primary care. The ACES Alto Minho (AM) comprises a geographic region of ten municipalities in the north region of Portugal with about 232 178 inhabitants in 2017: Arcos de Valdevez, Caminha, Melgaço, Monção, Paredes de Coura, Ponte da Barca, Ponte de Lima, Valença, Viana do Castelo, Vila Nova de Cerveira. Viana do Castelo is one of the most aged districts in Portugal. In 2018, the ACES AM Ageing Index was 220,3% and the old age dependency rate 39.2%, well above the mainland average (162.2% and 22.9 respectively). Moreover, the illiteracy rate (6.8%) was above the mainland average. For the 2016-18 triennium, the life expectancy at birth was 80.81 years, which is very similar to the national value (80.99) (86).

Form the intervention arm, pharmacies who fulfilled the following criteria will be invited to participate ( $\approx$ 9 pharmacies):

- Be affiliated in ANF (which represent 95% of the Portuguese community pharmacies).
- Location in the same municipality of the identified FHUs.
- With Sifarma® dispensing software ( $\approx$ 84% of all community pharmacies), to allow researchers to extract electronic data, on the acquisition of medicines by patients.
- With registered prescription sales from identified FHU

It is expected that the proportion of pharmacies accepting to participate in the intervention arm will be high (about 80% of the total invited) since this is an innovative health care service, involving multidisciplinary teams and collaborative interventions delivered by professionals from FHUs and Pharmacies. The recruitment strategy will be reinforced by several initiatives (e.g., telephone contacts

made by the principal investigator to the technical director of the invited pharmacies) to engage the participation of pharmacies.

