To avoid contamination bias, different geographic regions were chosen for the recruitment of control pharmacies and patients. The control selection involved the identification of the best-matching to intervention setting characteristics, firstly in terms of municipality sociodemographic characteristics and secondly in terms of existence of FHUs with similar traits of the intervention FHU (type and PPI consumption).

The following criteria was used to identify control regions for intervention study sites:

- 1) Municipalities with most similar characteristics of intervention sites (Arcos de Valdevez e Ponte da Barca), as estimated by three-dimensional normalized Euclidean distance, considering:
  - Municipalities *per capita* Purchasing Power (PP) ('Índice de Poder de Compra Concelhio per capita', 2019) (INE, 2022)
  - Municipality Aging ratio (AR) ('Índice de Envelhecimento no Concelho', 2020) (INE, 2022)
  - Municipality Illiteracy Rate (IR) ('Taxa de analfabetismo (%) por Local de residência', 2011) (Pordata, 2020)
- 2) FHUs from identified municipalities considering:
  - Contractual NHS type - Type "A" or "B" as the intervention units, as governance and funding models differ from FHU type (A or B).
  - Prescription volume of PPI per 1000 elderly ( $\geq 65$  y) in 2021, as FHU age pyramid (2022, data extracted in June 2022 from the site BI-CSP) most similar with the FHUs intervention. It was accepted a maximum absolute variation of 20% in comparison with the estimated value of the FHU intervention.

Additionally, it is planned to enroll more municipalities in the control arm to guarantee a similar number of participating pharmacies, as a lower pharmacy recruitment rate is expected in this group compared to the intervention. We expect an average pharmacy participating rate of about 20% (about  $\frac{1}{5}$  of the expected rate of the Intervention group) as previous found in others non-interventional studies conducted in pharmacies (source: CEFAR).

After identification of the FHUs, control pharmacies will be identified based on the same criteria used for intervention pharmacies. All the identified pharmacies will be invited to participate (≈60). Detailed information of the intervention and control municipalities and FHUs are depicted in Table 3.

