Secondly, after patient recruitment, a therapeutic profile will be drawn up and analyzed by the research team to list all medications taken by the patient in a regular basis and identify medication duplications and relevant drug-drug interactions (DDIs) (**Annex 7**). The therapeutic profile will be drafted based in extracted data from the pharmacies software regarding the sales associated to the patients' tax information number (NIF) and confirmed by patient self-report, via a telephone interview with the research team. DDIs will be assessed using Sifarma® software. In this telephone interview, the research team will confirm the use of the listed medications (prescription-only-medicines (POMs) and OTC). Further data for study purposes (e.g PROMs) will also be collected in the telephone interview (**Annex 8**). The final therapeutic profile and related safety information will then be sent to the community pharmacist by email (with access key) to be shared with the patient GP for clinical assessment.

Thirdly, the pharmacist will gather all the information, the PPI deprescribing recommendation and the therapeutic profile with identified moderate and severe DDIs provided by the research team and share with the GP. A specific paper case report form "Passaporte do utente" (**Annex 9**) will be used to exchange information between both pharmacists and GP.

Fourth, The GP with the information provided by the pharmacist and that in his/her medical records, will assess the PPI use and other reported safety issues (DDIs). The patient will be contacted by the GP to discuss the PPI deprescribing pertinence and strategy and, solve other possible medication related problems. All patients will be contacted by the GP preferably by telephone. A face-to-face consultation can be scheduled if the GP considers relevant. Fifth, the PPI withdrawal decision and adopted strategy agreed with the patient will be communicated to the pharmacist using the paper case report. Sixth, after the GP report to pharmacist, of the PPI withdrawal decision, pharmacist will contact the patient by telephone at 2 and 4 weeks, to monitor possible symptoms relapses, answer questions and if applicable, define with the patient a control-symptoms strategy (non-pharmacological) pre-agreed with the GPs under the designed intervention. The 4-week telephone interview will occur only on patients with PPI dose reduction or withdrawal indication. At the end of the withdrawal follow-up

---

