### **6.7. Study Follow-up**

Study follow-ups include 2 telephone calls, and electronic data extraction from the pharmacies dispense software at 3- and 6-months post recruitment. Telephone interviews are expected to last 10-15 minutes.

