#### *Primary outcomes*

The primary outcome is successful deprescription – discontinuation or decreased dose of PPI, defined as a statistically significant reduction in medication burden between the intervention and control group between baseline and 3- and 6-months follow-up ascertained by pharmacy medicine sales associated to the patients' NIF and confirmed by patient self-report.

Based on Deprescribing meaning (31), discontinuation of a PPI will be defined as:

- the lack of reported consumption assessed at 3 and 6-month follow-up, as well as the absence of initiation of another medicine from the same class, or;

- the reported dose-reduction assessed at 3 and 6-month follow-up, as well as the absence of initiation of another medicine from the same class.

The discontinuation/dose reduction rate among participants in the intervention arm will be compared to the discontinuation/dose reduction rate among participants in the control arm. In this way we will be able to determine the absolute rate of discontinuation attributable to the intervention.

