**Figure 3 - Average number of PPI sales per pharmacy in intervention Municipalities Jan 21-mai 22 (hmR sell-out data)**

On the other hand, official data collected from FHU BI reports 2021 indicates that, on average, in the 2 intervention FHUs, about 70% (72.4% in Arcos de Valdevez and 68.5% in Ponte da Barca) of PPI prescriptions were for elderly patients (65 years and older), suggesting that most all prescribed PPI sales could be potential eligible patients to be recruited for the study, with respect to the age criteria.

Analyzing routinely dispense data from the Pharmacies' software (June 2022/CEFAR), we observed that about 94% of the sales of PPI that were prescribed in these two FHU were sold on the pharmacies selected to participate in the study. This shows not only a very good regional PPI prescriptions (FHU) and sales (pharmacies) concentration, but also, in a more general term, that patients from these FHUs tend to acquire their medication locally. This is a good indication that once the recruitment is started, the number of potential eligible patients to invite for the study is high with respect to the pair FHU – Pharmacy criteria.

One thing that is important to notice is that only less than 1% of all PPI currently dispensed in these pharmacies are sold without a prescription (OTC medicines). This may include acute usage which is not eligible for entering the study. In this study the recruitment invitation will proceed to all eligible

patients carrying or not a prescription refill of PPI. This suggests that overall monthly PPI sales data could be a good starting point in the defining the recruitment period.

If the refusal rate would range between 50% and 75%, then it is expected that the recruitment period could last from 1 to 2 months to reach the estimated minimum sample size of the study.

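### Medicine counts and interactions start from pharmacy sales records, which may miss more purchases in controls because far fewer control pharmacies are expected to take part

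*Protocol*

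**What the plan says.** **Participation.** Protocol section 6.1 expects intervention pharmacies to accept at a rate of "about 80% of the total invited", out of roughly 9. For the control arm it says "We expect an average pharmacy participating rate of about 20" per cent, out of roughly 60.

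**Sales source.** The dispensing software is an entry criterion for pharmacies "to allow researchers to extract electronic data, on the acquisition of medicines by patients". Section 6.7 plans "electronic data extraction from the pharmacies dispense software at 3- and 6-months post recruitment". No other patient-level sales source is described.

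**Regular medicines and interactions.** In section 6.5 the therapeutic profile is drafted from sales linked to the patient's tax number. In the telephone interview, "the research team will confirm the use of the listed medications". Table 5 repeats this order for other regular medicines at baseline and 6 months (pharmacy software, then interview), without separating the arms. For interactions it names pharmacy software alone.

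**PPI status.** Section 6.8 has the primary outcome "ascertained by pharmacy medicine sales associated to" the patient's tax number and backed by self-report. Table 5 (PPI continuous use) and section 6.17.4.1 say the same. The definitions that follow in section 6.8 rest on consumption or dose as reported by the patient, and section 6.15.4 requires reported PPI use at 6 months.

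**The concern.** A list that begins with sales and is then confirmed can lose entries that the patient denies. As described, it does not gain medicines that never entered the extract. If the extract covers the study pharmacies only, a purchase elsewhere in the municipality usually stays visible for an intervention patient and usually disappears for a control patient.

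Controls could then appear to take fewer medicines, to have polypharmacy less often and to have fewer interactions. An interaction is lost when either medicine of the pair is missing. A control patient who moves pharmacy during follow-up could show a drop in medicines that did not happen. These are secondary outcomes comparing the two arms, and purchases not recorded during the study cannot be recovered afterwards. Section 7 does not list unequal capture among the limitations.

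**Working it through.** **1. The plan's own figures.** Expected participating pharmacies are 9 × 0.80 = 7.2 (intervention) and 60 × 0.20 = 12 (control). Per municipality, two intervention municipalities give 9/2 = 4.5 invited and 7.2/2 = 3.6 taking part. Eleven control municipalities give 60/11 ≈ 5.5 invited and 12/11 ≈ 1.1 taking part. Section 6.1 also puts the control rate at about one fifth "of the expected rate of the Intervention group". In fact 20/80 is one quarter, and one fifth of 80% is 16%. That is a separate, minor slip.

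**2. Captured share of a patient's purchases.** Let s be the share bought at the recruiting pharmacy (always captured) and p the participation rate. Assume the remaining purchases are spread evenly over the invited pharmacies and that only participating pharmacies are extracted.

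Captured share = s + (1 − s) × p; gap between arms = (1 − s) × (0.80 − 0.20).

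| s (assumed) | Intervention | Control | Gap |
|---|---|---|---|
| 0.70 | 94% | 76% | 18 points |
| 0.80 | 96% | 84% | 12 points |
| 0.90 | 98% | 92% | 6 points |
| 1.00 | 100% | 100% | 0 |

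The protocol gives no value for s. The nearest figure, in section 6.11, is approximate: "94% of the sales of PPI that were prescribed in these two FHU were sold on the pharmacies selected to participate in the study". It concerns recruitment feasibility, counts all selected pharmacies before refusals, and has no control counterpart.

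These are shares of purchases. Over a six-month window a medicine drops off the list only if every purchase of it falls outside the extract, so the gap in medicines missed can be smaller.

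**3. Change from baseline.** At s = 0.80, if each medicine had that chance of being listed, a stable under-capture would show a true drop of one medicine as 0.96 in the intervention arm and 0.84 in controls. The missing level cancels, but the scale does not. A fixed threshold such as five medicines, or a change of pharmacy after baseline, does not cancel either.

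**4. PPI status, only if sales decided.** Exact enumeration of the two-sided Fisher test for 10% versus 30% reproduces the planned size: power 0.8977 at 88 per group and 0.9017 at 89. Now assume that 10% of continuing users move to another local pharmacy and that sales alone decide:

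- intervention: 0.30 + 0.70 × 0.10 × 0.20 = 0.314
- control: 0.10 + 0.90 × 0.10 × 0.80 = 0.172
- difference: 14.2 points, with Fisher power about 54% at 89 per arm

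If interviews correct 80% of these errors, the rates are about 30.3% and 11.4%, the difference 18.8 points and the power about 85%. If interviews correct all of them, the 20 points and 90% power return. What matters is therefore which source prevails.

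**The case against.** The strongest reply concerns the primary outcome. A reader might infer that missed control sales would be counted as PPI discontinuation. The documents do not support that as it stands. Discontinuation is defined through what the patient reports, the primary analysis needs reported use at 6 months, and the same interviews run in both arms. The index PPI is also known for every patient, since recruitment is triggered by a PPI being dispensed. This stands. What remains is that other places ascertain the outcome by sales backed by self-report, and no rule covers disagreement.

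A reader might also take 80% and 20% as the shares of purchases captured. They are pharmacy acceptance rates, and each patient is recruited at a pharmacy that has just dispensed to them. This stands, and it is why the range above is stated for loyal patients. Likewise, the limit to participating pharmacies is inferred and is nowhere stated.

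On medicines and interactions, section 6.8 runs the software's alert system on all medicines taken, so Table 5 may be naming the checking tool and not a sales record. Section 7 relies on an interviewing pharmacist to help validate the medicines, and the telephone questionnaires (Annexes 8 and 14) may already ask about unlisted ones. Outcomes are changes from baseline, so stable under-capture partly cancels. All this lowers the likely size. It does not remove the point, because the text describes a list built from sales and then confirmed, and the interaction check can only see what is on that list.

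Sensitivity analyses can be left to the statistical analysis plan. The data source in Table 5 and the definition of the primary outcome are fixed by the protocol itself.

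**Conclusion.** The concern holds for medicine counts, polypharmacy and interactions: followed as written, the method may miss more purchases in controls. If 80% to 90% of purchases are made at the recruiting pharmacy, the gap in captured purchases is about 12 to 6 points. It is larger with less loyalty and nil if patients use one pharmacy only. This rests on three assumptions: extraction limited to participating pharmacies, even spread of the remaining purchases, and interviews that do not add unlisted medicines.

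For PPI status there is an unresolved wording conflict and no demonstrated bias. The effect on the primary outcome arises only if sales override the patient's report, and the drop to 14.2 points illustrates that condition alone. The point merits correction before data collection because the remedy is cheap and lost purchases cannot be restored. It does not call the design or the sample size into question.

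**What to change.** - In section 6.5 and Table 5, make an open interview list of all current medicines and doses, asked identically in both arms at baseline and 6 months, the source for medicine counts and for the interaction check. Use the sales extract as a prompt.
- Reconcile the sales-based wording (section 6.8, Table 5, section 6.17.4.1) with the reported-use definitions in section 6.8 and the requirement in section 6.15.4. State that reported PPI use decides the primary outcome in both arms, and that absence of sales in the extract is never sufficient alone for discontinuation.
- State which pharmacies the extract covers.
- Report sales capture, and disagreement between sales and self-report, by arm, and list unequal capture in section 7.

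The cost is slightly longer calls, in interviews already planned, and more reliance on self-report.

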**Table 3 - Details of the intervention and identified municipalities and control FHUs**

| Group        | FHU name and Type          | N.elderly
Registered at
FHU | N. GP (BI-
CSP, 2022) | Municipality / District              |
|--------------|----------------------------|-----------------------------------|--------------------------|--------------------------------------|
| Intervention | Uarcos - B                 | 3546                              | 7                        | Arcos de Valdevez / Viana do Castelo |
|              | Terra da Nóbrega - A       | 3573                              | 10                       | Ponte da Barca / Viana do Castelo    |
|              | Senhora da Graça – B       | 1911                              | 11                       | Mondim de Basto / Vila Real          |
|              | Penela -B                  | 1910                              | 4                        | Penela / Coimbra                     |
|              | Baião – B                  | 1812                              | 6                        | Baião / Porto                        |
|              | Lethes – B                 | 3436                              | 9                        | Ponte de Lima / Viana do Castelo     |
|              | Mais Saúde - B             | 2071                              | 5                        |                                      |
|              | D’As Terras de Lanhoso – B | 2797                              | 7                        | Póvoa de Lanhoso / Braga             |
| Control      | Prado – B                  | 12339                             | 6                        | Vila Verde / Braga                   |
|              | Pró-Saúde - B              | 6976                              | 5                        |                                      |
|              | Vida+ - B                  | 12152                             | 7                        |                                      |
|              | Nova Mateus - A            | 1889                              | 8                        | Vila Real / Vila Real                |
|              | Fénix – A                  | 3266                              | 7                        |                                      |
|              | Corgo - A                  | 3111                              | 6                        |                                      |
|              | Raia Maior – A             | 2043                              | 5                        | Campo Maior / Portalegre             |
|              | Costa Campos – A           | 1527                              | 2                        | Sobral de Monte Agraço / Lisboa      |
|              | Remo – A                   | 2901                              | 6                        | Reguengos de Monsaraz / Évora        |
|              | Amoreira – A               | 3310                              | 8                        | Elvas / Portalegre                   |
|              | Uadiana - A                | 2052                              | 6                        |                                      |

General practitioners (GP); Family Health Units (FHU)

## **6.2. Pharmacy Invitation / Recruitment**

A personalized invitation will be sent to the eligible community pharmacy owners in the geographical areas of the identified FHUs. Community pharmacies that intend to participate will be asked to fill in a participation form listing the participating pharmacists, correspondent pharmaceutical society number, and the name of the pharmacist(s) who will be responsible for the study implementation and procedures of the study in the community pharmacy.

The community pharmacies which agree to participate (intervention and control) will be trained in the study procedures by the research team (for more detail see sub-section “training”).

Each community pharmacy will be asked to recruit at least 10 patients.

### **6.2.1. Retention Strategies**

To maximize retention of pharmacies and pharmacy staff, follow-up phone calls and regular recruitment achievements email reports will be sent by the study research team to each pharmacy.

## **6.3. Study population and Eligibility criteria**

The study population comprises community-dwelling older adults ( $\geq 65$  years old) with a long-term use ( $>8$ -week use) of any PPI, recruited from community pharmacies.

PPI medication was chosen for this trial, based on its high consumption in Portugal (PPI was among the top 10 more consumed medicines in ambulatory care on Portugal in 2019) and among these population (51), availability as OTC medicines allowing an easier access to them, health professionals report of PPI as one of the preferential groups of medicines to deprescribe (77), and on the following high-evidence criteria / recommendations:

- 2019 Updated Beers Guidelines for Inappropriate Prescription (45)
- The EU (7)-PIM list (46)
- Portuguese PPI- Directorate-General for Health clinical guidance (87)

All inclusion and exclusion criteria will be followed by the community pharmacies’ staff to ensure that the patient is eligible for the study (**Annex 1**-enrollment guide). If a patient is eligible, the pharmacist

will explain the aim of the study, invite the patient to participate and sign the Informed Consent form (ICF) (**Annex 2**), before any intervention and/or data collection.

Patients who fulfill the inclusion criteria, have no exclusion criteria, agree to participate, and sign the ICF will be enrolled consecutively for a two-month period (can be extended if needed to achieve the sample size). Both groups (intervention and control) will undergo a 6-month follow-up study period.

